#### DEHP-d4 Exposure Concentration

The concentration of DEHP-d4 in the e-liquid (percentage by weight) was set at a value that produced DEHP-d4 concentrations for participant exposures (C_exp_, mg/m^3^) at or below the Swiss occupational exposure limit (OEL) for DEHP (2 mg/m^3^) [50]. The OEL is set at concentrations that, based on available scientific data, should not produce health effects in workers exposed to a substance in the air every day for a workweek throughout their working lifetime (in Switzerland: 8 hours per day, 5 days a week, for 40 years). C_exp_ was calculated based on the following equation:

where M_puff_ was the mass of DEHP-d4 in the aerosols generated in a puff by ENDS coupled with the vaping machine (µg per puff), p was the number of puffs per minute that an ENDS user would consume per minute (puff per minute), V_tidal_ was the human mean tidal volume (0.5 L of air per inhalation [51,52]), and IE was the number of inhalations/exhalations per minute.

### Part II: Human Toxicological Study Protocol

#### Participant Sample Size and Selection

A maximum of 10 participants (N=10) will be recruited for repeated exposure to DEHP. Participants who are interested in the study will be checked for eligibility through a short general health questionnaire. These questions are about smoking status, age, BMI, alcohol consumption, general health status, and current job (to exclude the possibility of exposure to phthalates at work). The eligibility criteria are described in Textbox 1.

Inclusion and exclusion criteria approved by the Ethical Committee. The inclusion criteria “able to understand the procedure” mean the presumed ability of the participants to understand or discern the written and oral explanations during the first visit. This capability will be assessed as follows: by asking the participants to repeat what they understood about the study; by asking questions to the participants and assessing their answers (eg, studied molecules, number of visits, right to accept or reject participation in the study, etc).
**Inclusion criteria**
Aged between 18 and 65 years old.Men and nonpregnant women (negative pregnancy test).Nonsmoker (vaping is authorized).Not under a medical regime.BMI between 18 and 25.Not exposed to phthalates at work.Able to understand the procedure.Has signed the consent form for research project participation.

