Children and adults living in industrialized countries are estimated to spend around 17-19 hours and 21 hours per day indoors (ie, at home and in the working environment), respectively [26]. There is considerable concern regarding phthalate exposures because several epidemiological studies have shown associations between exposures to some phthalates and retarded male reproductive development [11,12], altered semen quality [13,14], endometriosis [27,28], and respiratory diseases in children [29]. When inhaled, phthalates can reach the alveoli, be absorbed into the blood, and then be distributed to potential target tissues, where they may trigger an effect. Therefore, absorption rates (ie, rate at which the molecule enters blood), internal doses (ie, parent compound concentrations in blood), as well as metabolic and elimination rates (ie, rate of metabolites’ formation and elimination, usually in urine), are important toxicokinetic parameters to accurately determine the total exposures in the human body and, thus, potential risks to the population. Although urinary metabolite ratios were reported to be different between humans and animals [30-34], these toxicokinetic parameters have not been studied in humans exposed to phthalates through inhalation as a single exposure route. The few human toxicokinetic studies conducted with phthalates were mainly after ingestion [35-38]. A total of 2 human studies have been conducted on phthalates, including simultaneous exposure through the skin and inhalation routes [39,40]. These studies only provided estimated toxicokinetics (absorption, distribution, metabolism, and excretion [ADME]) for the inhalation route. Since inhalation is considered a significant indoor route of exposure for some phthalates [41], toxicological studies need to be performed to understand phthalates’ ADME through this exposure route. However, a procedure to expose healthy participants to SVOCs is lacking due to the absence of devices for human studies with SVOCs through inhalation. We aim to fill these gaps by describing the required steps to obtain human ADME data after inhalation. The SVOC selected in this study is DEHP, a model SVOC due to its major presence in the indoor environment (air and dust) and human populations (urine). This study is divided into 2 parts. Part I describes the dosing procedure and how to generate aerosols at environmentally relevant phthalate concentrations with a device suitable for chronic inhalation exposure. Airborne phthalate aerosols will be produced based on the technology of commercially available “electronic nicotine delivery systems” (ENDS), which have proven efficacy in generating aerosols for human use [42,43]. ENDS are generally used to generate nicotine or flavored aerosols from highly viscous liquids such as glycerol (viscosity=1412 mPa·seconds) making this technology suitable for viscous chemicals such as some phthalates. Part II provides the study protocol for participants exposed to ring-deuterated DEHP for several days. Unisanté has strong expertise in toxicological studies with healthy participants and has adapted its protocols for repeated, at-home exposure. We will show the results of the first participant here as proof of concept.

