**Exclusion criteria**
Aged 18 years or younger.Pregnant women.Smoker (cigarette, pipe, and cigar smoker).Under a medical regime.BMI below 18 or greater than 25.Exposed to phthalates at work.Not capable of understanding the procedure.Has not signed the specific consent form for research project participation.

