#### Participant Timeline

The flowchart in Figure 3 shows the steps from participant screening and visits through exposure periods until data analysis. Briefly, an initial contact with the participant will be established by email to explain the study and obtain informed consent. Then, a phone call will be made to check if the inclusion and exclusion criteria are met and to get answers for a short general health questionnaire. If the inclusion criteria are met, the participant will be invited for a first visit. At this visit, the participant will sign the written informed consent. Women of reproductive age will also undergo a pregnancy test. Then, the participant will be given an aerosol-forming device and, after being instructed on how to use the device, will undergo the first inhalation exposure under the supervision of a research team member (see “Participant Exposure” section). A blood and urine sample will be collected before the first exposure (baseline) and will serve as baseline concentrations (control). Blood will be drawn again 30 minutes after the first exposure. Then, participants will follow the expected vaping schedule with DEHP-d4-spiked e-liquid and collect spot urine samples 4 times throughout the day (morning, midday, evening, and night) for the 4 days of exposure. Blood and urine collecting times are shown in Multimedia Appendix 1.

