## Appendix

Multimedia Appendix 1 Blood and urine sampling design. The exposure period is shown in grey. On day 1, blood and urine will be taken to provide baseline data (controls). Then, the first exposure starts and will be repeated twice a day, in the morning and in the evening. On day 3, participants return to our facilities to hand out day 1 to day 3 urine samples and for blood sampling. The last exposure is on day 4. On day 5, participants hand out urine samples from day 4 and the morning of day 5; a postexposure blood sample is collected at our facilities.

Multimedia Appendix 2 SCAHT_Experts_Outcome.

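### The approved eligibility criteria exclude pregnancy but not breastfeeding, despite the article's own developmental concern, and two sections differ on which women need a negative test

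*Protocol article*

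**What the plan says.** Participant Sample Size and Selection introduces Textbox 1 with the words "Inclusion and exclusion criteria approved by the Ethical Committee". The textbox holds eight inclusion and eight exclusion items. The relevant inclusion items are "Aged between 18 and 65 years old" and "Men and nonpregnant women (negative pregnancy test"; the matching exclusion item is "Pregnant women". Breastfeeding is not mentioned there or anywhere else in the article.

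The same section describes the eligibility questionnaire: "These questions are about smoking status, age, BMI, alcohol consumption, general health status, and current job". Participant Timeline has the criteria checked by phone before the first visit. For that visit it adds: "Women of reproductive age will also undergo a pregnancy test". The first inhalation follows at the same visit.

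The Abstract describes two exposures a day over four days, and Multimedia Appendix 1 confirms the end point: "The last exposure is on day 4". Participants return on days 3 and 5, and no further pregnancy test is described at those visits.

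On why phthalates matter, the Abstract names endocrine disruption. The Introduction cites "associations between exposures to some phthalates and retarded male reproductive development" and, in the same sentence, respiratory disease in children.

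**The concern.** By excluding pregnant women, the sponsor has already judged that a developing child should not be exposed through the mother. The listed criteria carry that judgement only as far as pregnancy. A breastfed infant raises the same kind of question, and no listed item addresses it.

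What is at stake is participant and infant safety, and clarity at screening. Someone applying Textbox 1 as printed has no ground to decline a breastfeeding volunteer and no prompt to ask. Separately, Textbox 1 and Participant Timeline give screening staff different instructions about women past reproductive age.

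**Working it through.** No arithmetic applies to the main point. It depends on no sample-size, variance or effect figure, and the plan states no figure to reproduce. The check is a comparison of sections.

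**1. Can a breastfeeding woman pass every item?** Take a breastfeeding woman aged 18 to 65 with a negative test, who does not smoke, has a BMI in range, has no phthalate exposure at work, understands the procedure and has consented. Two items need a closer look:
- Pregnancy (inclusion and exclusion): she is not pregnant and tests negative, so she passes.
- Medical regime (inclusion and exclusion): the term is undefined and does not name breastfeeding, so on its face she passes.

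She meets all eight inclusion items and triggers none of the eight exclusion items.

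**2. Would the questionnaire catch her?** Its listed topics are smoking, age, BMI, alcohol, general health and job. General health might prompt a volunteer to mention breastfeeding, but nothing listed asks for it, and no criterion would make the answer decisive.

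**3. Does the exposure limit answer the concern?** DEHP-d4 Exposure Concentration sets the concentration at or below the Swiss occupational limit. It explains that limit in terms of workers exposed over a working lifetime and does not say that it covers a fetus or a breastfed infant. The Abstract adds that human data on the fate of inhaled compounds of this class are nearly absent, and the Discussion leaves accumulation open. The article thus gives no ground for treating the infant as unexposed.

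**4. Who is tested?**
- Textbox 1: a negative test is attached to women without an age qualifier, and ages up to 65 are admitted.
- Participant Timeline: the test is given to women of reproductive age.

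An older woman handled under Participant Timeline has no test result to set against Textbox 1 as printed. The difference concerns only women past reproductive age.

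**5. What can the test show?** It is done at the first visit, before the first inhalation. With 2 exposures a day over 4 days, 2 × 4 = 8 exposures follow it. A test on day 1 cannot exclude a conception too recent to detect, or one on days 1 to 4. This is a matter of logic and needs no assumed detection lag.

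**6. Who could still be affected?** The maximum is 10 participants and 5 were enrolled as of May 2023, so at most 10 − 5 = 5 places remained at that date. How many would go to women is not stated.

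**The case against.** The strongest objection is that the article condenses a longer protocol (Version 8) and refers to an approved information sheet and consent forms, none of which is shown. Precautions may sit there. This stands for conception and contraception, which are commonly handled in such documents. It is much weaker for breastfeeding as a criterion, because Textbox 1 is offered as the approved criteria and not as a selection from them.

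A reader might infer that a single pregnancy test is the only safeguard. The document does not support that: pregnancy is a separate exclusion item, and the phone call checks the criteria before the first visit. There is a declared-pregnancy screen followed by a test.

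A reader might also turn the test's limits into a count of days at risk. The article gives no detection lag, so any such count rests on an outside assumption. It would be a calendar window and not a risk.

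On harm, the Introduction cites associations for some phthalates, and that sentence does not name DEHP. The article does not discuss transfer into milk. Exposure is short, with a mean of 1.4 μg DEHP-d4 per puff on the vaping machine and a target at or below the occupational limit. These facts limit the likely harm and belong in any judgement of weight. They do not supply the missing criterion.

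Finally, the parenthesis in Textbox 1 can be read as saying how non-pregnancy is shown, with Participant Timeline saying for whom. That is a fair reading. To infer that older women would be wrongly refused, or enrolled as protocol deviations, takes a very literal one.

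**Conclusion.** The point holds for breastfeeding. Under the criteria as printed, a breastfeeding woman with a negative test is eligible, although the article's own rationale rests on endocrine and developmental concerns and it describes its exposure cap only for workers. This should be corrected because it affects who is exposed. It changes no estimate or analysis, and no probability of harm can be derived from the document. The conclusion assumes that Textbox 1 is the complete list, as its heading indicates.

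The mismatch over who is tested is real but minor.

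Very recent conception, or conception during exposure, is a matter for the sponsor to verify in the full protocol and information sheet. That those documents contain no such safeguard cannot be established from the article.

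**What to change.** - Add breastfeeding to the exclusion criteria in Textbox 1, and add a matching item to the existing screening questionnaire.
- Reconcile Textbox 1 with Participant Timeline on which women need a negative test. One qualifying phrase is enough.
- Check that the full protocol and information sheet address very recent conception and conception on days 1 to 4. A rule demanding that pregnancy be impossible, confirmed by asking at the first visit, would not work: a question cannot establish the absence of an undetected or later pregnancy, and read literally the rule could exclude many women.

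The cost is one amendment to the criteria and one questionnaire item, with no change to the analysis. A few volunteers may be excluded. In a study of at most 10, where gender is a planned effect modifier, that loss is not negligible and should be weighed openly.

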**Exclusion criteria**
Aged 18 years or younger.Pregnant women.Smoker (cigarette, pipe, and cigar smoker).Under a medical regime.BMI below 18 or greater than 25.Exposed to phthalates at work.Not capable of understanding the procedure.Has not signed the specific consent form for research project participation.

#### Participant Timeline

The flowchart in Figure 3 shows the steps from participant screening and visits through exposure periods until data analysis. Briefly, an initial contact with the participant will be established by email to explain the study and obtain informed consent. Then, a phone call will be made to check if the inclusion and exclusion criteria are met and to get answers for a short general health questionnaire. If the inclusion criteria are met, the participant will be invited for a first visit. At this visit, the participant will sign the written informed consent. Women of reproductive age will also undergo a pregnancy test. Then, the participant will be given an aerosol-forming device and, after being instructed on how to use the device, will undergo the first inhalation exposure under the supervision of a research team member (see “Participant Exposure” section). A blood and urine sample will be collected before the first exposure (baseline) and will serve as baseline concentrations (control). Blood will be drawn again 30 minutes after the first exposure. Then, participants will follow the expected vaping schedule with DEHP-d4-spiked e-liquid and collect spot urine samples 4 times throughout the day (morning, midday, evening, and night) for the 4 days of exposure. Blood and urine collecting times are shown in Multimedia Appendix 1.

**Figure 3 figure3:**
[figure not shown]
Flowchart of recruitment, screening, visits, interventions, sampling, and analysis. SVOC: semivolatile organic compound.

#### Blood and Urine Analysis

The Laboratory of Clinical, Forensic, and Environmental Toxicology, University Hospital of Liege, will determine DEHP-d4 and its metabolites concentrations in blood. The quantified metabolites will be deuterated mono(2-ethylhexyl)phthalate (MEHP-d4), deuterated mono(2-ethyl-5-hydroxyhexyl)phthalate (5OH-MEHP-d4), and deuterated mono(2-ethyl-5-oxohexyl)phthalate (5oxo-MEHP-d4). The Institute for Prevention and Occupational Medicine of the German Social Accident Insurance, Institute of the Ruhr-Universität Bochum (IPA), will quantify DEHP-d4 metabolites in urine, as described in Koch et al [53]. The metabolites quantified by the IPA laboratory will be MEHP, 5OH-MEHP, 5oxo-MEHP, and mono(2-ethyl-5-carboxypentyl)phthalate (5cx-MEPP).

#### Participant Exposure

Participants will use the portable aerosol-forming device themselves, first in our facilities (day 1) and then at home (days 1-4). The e-liquid will have a PG/VG ratio of 50/50 with 1% (w/w) ethanol and 0.02% (w/w) DEHP-d4. The participants enrolled in the study will press a button on the ENDS battery. The coil will heat the e-liquid, generating an aerosol with DEHP concentrations less than or equal to the OEL.

The e-liquid will be prepared in advance for DEHP-d4 quantification analysis and will be stored at room temperature during the exposure week. A fraction of the e-liquid will be sent to the analytical laboratory of EPFL to confirm the DEHP-d4 concentration in the e-liquid, and the rest will be frozen at –20 °C until use. On the day of the first exposure to DEHP, the e-liquid will be defrosted. A vial with a weighted amount of e-liquid sufficient for 1-week exposure (ie, reserve) will be prepared for each participant. This vial will be stored at room temperature at the participant’s place, where they will use it to refill the ENDS e-liquid tank when needed. Therefore, a stability test is required to verify DEHP-d4 concentration after several days of storage at room temperature. This step is also important for the relevance of the study. On day 5, the participant will return the ENDS and the e-liquid vial, which will be weighed to calculate the exact amount of e-liquid puffed by the participant, hence the amount of puffed DEHP-d4.

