## Discussion

We developed a method to generate aerosols containing controlled concentrations of SVOCs of toxicological relevance (ie, DEHP in this study) for controlled human exposure studies. Aerosols were generated by a portable and easy-to-use device (ENDS). Our results showed that DEHP in the e-liquid was stable for the duration of the study and that ENDS-generated aerosol particles were in the respirable range. Therefore, DEHP was likely to reach the alveoli, be absorbed, and enter the systemic circulation. Knowledge of human toxicokinetics after SVOC aerosol inhalation exposures will help regulatory agencies set new exposure limits and new requirements for toxicity reporting from manufacturers or suppliers because the data are human data instead of animal data. Some e-liquid leaking occurred with our first participant. This will be prevented by asking the next participants to keep the ENDS at home in a vertical position.

In the near future, our portable aerosol device will be used to study biomarkers of phthalate exposure in humans and the influence of these chemicals on a panel of readouts related to human health. We believe that this protocol with a take-home device has an easy approach, and we therefore anticipate that participant compliance rates to the exposure protocol will be high. The potential limitations of this protocol are the risks of missing part of the dose in blood and urine because only DEHP metabolites, not the parent compound, are quantified in these fluids, and participants are asked for spot urine samples, not 24-hour urine collection for every day of exposure. We hope this protocol will help other researchers design human inhalation studies of environmental substances that can contribute to the large data gap that exists today.

The results of this study will add new and important human data on the toxicokinetics of SVOCs such as DEHP upon repeated, inhalation-only exposures. Understanding phthalate toxicokinetics upon repeated exposure will help researchers understand possible phthalate accumulation in the body (if any) and improve models estimating internal exposures from external exposures, as well as interpret biomonitoring results from the general population, where urine is often collected at different times.

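### The results are to be presented as inhalation-only, but participants handle DEHP-d4 liquid at home and skin or oral uptake could be neither detected nor excluded

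*Protocol article*

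**What the plan says.** The Introduction of the protocol article sets out the gap: "these toxicokinetic parameters have not been studied in humans exposed to phthalates through inhalation as a single exposure route". It notes two earlier human studies "including simultaneous exposure through the skin and inhalation routes" and says that these gave only estimates for the inhalation route. The Discussion then presents the coming results as "new and important human data on the toxicokinetics of SVOCs such as DEHP upon repeated, inhalation-only exposures".

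Under Participant Exposure, the first session takes place at the study site and later ones at home, up to day 4. Participants keep a reserve vial of the liquid (0.02% w/w DEHP-d4) at home, "where they will use it to refill the ENDS e-liquid tank when needed".

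The Discussion reports: "Some e-liquid leaking occurred with our first participant". The remedy follows: "This will be prevented by asking the next participants to keep the ENDS at home in a vertical position". The limitations named there are metabolite-only measurement and spot urine. Uptake by a route other than inhalation is not among them.

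The Abstract and the E-Liquids section give the deuterium label one purpose: to tell study exposure from environmental or laboratory DEHP.

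**The concern.** A single exposure route is what sets this study apart from the earlier ones, so the article should claim it only as far as the design can support it. Liquid and aerosol contain the same labelled compound, and the laboratories measure labelled metabolites whatever the route of entry. If liquid reached the skin or mouth during a refill or after a leak, the labelled metabolites would be read as inhaled dose.

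The analysis fits absorption and elimination rates for each participant. An unrecorded input at an unknown time and by another route could distort an individual fit, and nothing in the described sampling would reveal it. With at most 10 participants, one affected course is a tenth of the data. Vertical storage addresses leaking, but not contact while the tank is being refilled.

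**Working it through.** **Inputs from the article.** Aerosol concentration 25.4 (SD 3.4) mg/m³ and 1.4 (SD 0.2) µg DEHP-d4 per puff (Results, Mass Balance and Aerosol Concentrations); puff volume 55 mL (Aerosol Generation and Vaping Machine); liquid at 0.02% w/w (Participant Exposure); two exposures a day for four days, so 8 sessions (Abstract).

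**Inputs assumed.** Drop of 20-50 mg; 10 puffs per session, varied from 5 to 36; uptake of 1%, 10% or 100% of the liquid in contact. The text at hand gives none of these.

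**1. The article's own figure.** Mass per puff = concentration × volume = 25.4 µg/L × 0.055 L = 1.397 µg; SD = 3.4 × 0.055 = 0.187 µg. The stated 1.4 (0.2) µg is reproduced.

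**2. Label in the liquid.** 0.02% w/w = 0.2 µg per mg. One puff therefore carries the label of 1.4 / 0.2 = 7 mg of liquid.

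**3. One drop in puffs.** 20 mg × 0.2 = 4 µg and 4 / 1.4 = 2.9 puffs; 50 mg × 0.2 = 10 µg and 10 / 1.4 = 7.1 puffs.

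**4. One drop against the whole course.** Puffed mass = 8 × 10 × 1.4 = 112 µg.
- 100% uptake: 4 / 112 = 3.6% to 10 / 112 = 8.9%.
- 10% uptake: 0.4% to 0.9%.

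**5. Sensitivity to puffs per session, for a 50 mg drop.**

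| Puffs per session | Puffed mass, 8 sessions (µg) | 1% uptake | 10% uptake | 100% uptake |
|---|---|---|---|---|
| 5 | 56 | 0.18% | 1.8% | 18% |
| 10 | 112 | 0.09% | 0.9% | 8.9% |
| 20 | 224 | 0.04% | 0.45% | 4.5% |
| 36 | 403 | 0.02% | 0.25% | 2.5% |

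The denominator is the mass puffed, not the mass retained in the airways. If part of the aerosol is exhaled, the share relative to retained dose would be larger.

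**6. Which samples could be affected.** Baseline blood and urine precede any exposure. The blood sample 30 minutes after the first exposure follows a supervised session. Home refilling can affect neither. It could affect samples from the home phase onward: later spot urine and the day 3 and day 5 blood.

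**The case against.** The strongest reply is that the article shows an opportunity and not an event. It reports no skin contact, no swallowing and no uptake by another route. The leak is reported without an amount and is not said to have reached the participant. Refilling is conditional on need. Handling and spill instructions may well stand in the full protocol or the information sheet, and an article need not repeat them. All of this stands.

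Four stronger readings are tempting, and the article does not support them:

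- **That skin and oral uptake has in fact mixed into the data.** Nothing reported shows this.
- **That one drop is a large part of the dose.** Set against a single 10-puff session (14 µg), 4-10 µg is 29-71% at full uptake and about 3-7% at 10%. This compares one accident with one session and rests on assumed drop size, puff count and uptake. Over the course, step 4 applies. The single-session comparison shows only that the timing of one input might matter to an individual fit.
- **That the design repeats the mixed exposure of the two earlier studies.** Incidental contact while filling a device is not the same as simultaneous exposure by two routes.
- **That a swallowed share of the aerosol is established.** The article describes mostly respirable particles and gives no swallowed fraction.

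It can also be said that removing the vial would not stop a tank from leaking, and that tank capacity is not given, so a single fill might not last to day 3. That is why staff filling can only be conditional.

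What the reply does not remove is that the label cannot tell routes apart, that the inhalation-only claim is unqualified, and that the stated limitations do not mention this.

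**Conclusion.** The point holds as one about what can be claimed and checked. The article asserts a single route, lets participants handle the labelled liquid, reports one leak, and describes no measurement that could detect or exclude uptake by another route. The documents support neither a finding that such uptake took place nor a finding that the kinetics are biased.

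The size is unknown. On the assumptions above, one 20-50 mg drop amounts to roughly 4-9% of the puffed mass over eight 10-puff sessions if all of it is absorbed, and to less than 1% at 10% uptake. Varying the assumed puff count and uptake for a 50 mg drop gives 0.02% to 18%. A larger contact would scale in proportion.

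This is a low-cost improvement that protects the study's central claim. With 5 of at most 10 participants enrolled by May 2023, it could still be applied to those to come.

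**What to change.** 1. At the existing day 3 and day 5 visits, ask about and record any leak, spill, or skin or mouth contact with the liquid, with date and time. For participants already completed, note what is known, including the first participant's leak.
2. Repeat the individual absorption and elimination fits, and the comparison of rates, without affected periods or participants, and report both sets. Decide beforehand how long after a contact a period counts as affected. Where that cannot be bounded, leave out the participant from that time on.
3. In the Discussion, qualify inhalation-only, for example as exposure by mouthpiece inhalation with other uptake neither measured nor excluded. Add undetectable non-inhalation uptake to the limitations. This stays necessary after steps 1 and 2, because unnoticed contact will not be reported.
4. Where tank capacity allows, have staff fill the tank on day 1 and top it up on day 3, so that home refilling is kept to a minimum. At 7 mg per puff, eight sessions of 10-20 puffs (assumed) use 8 × 10 × 7 = 560 mg to 8 × 20 × 7 = 1,120 mg. The 7 mg assumes that DEHP-d4 leaves the liquid in proportion, so liquid use per puff and tank capacity should be checked first. A tank that ran dry would cost a session.

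The cost is a few minutes of staff time at visits already planned, a change of wording, and possibly some data lost from the sensitivity analysis, which would be noticeable with at most 10 participants.
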